#### Sample size consideration

2.2.6

This trial employed a randomized, double-blind, parallel-group design. Sample size calculations were based on the primary efficacy indicators, estimated as the change in PR from baseline at week 12 of treatment. Based on our preclinical pilot study, acupuncture treatment for asthenozoospermia yielded a mean percentage change of 6.6 ± 4.2, while sham acupuncture treatment showed a mean change of 3.2 ± 3.7. With α = 0.025 (one-tailed) and β = 0.1 (90% power), the critical value was estimated as δ = 5% (1/5 of the mean change). With a 1:1 trial-to-control ratio, each group requires 30 participants. Strict quality control during the trial will limit the loss to follow-up rate to 20%, resulting in a total study sample of 72 participants, and finally 36 in the trial group and 36 in the control group.

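### At the stated 20% loss, 36 per group leaves about 29 evaluable participants, not the 30 the plan requires (a small inconsistency)

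*Protocol article*

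**What the plan says.** The sample size is set out in section 2.2.6 of the protocol article and is based on the change in progressive motility from baseline to week 12. The pilot figures are that "acupuncture treatment for asthenozoospermia yielded a mean percentage change of 6.6 ± 4.2" and that "sham acupuncture treatment showed a mean change of 3.2 ± 3.7". The error rate is 0.025 one-sided and the power 90%. The section also gives a δ of 5%, described as one fifth of the mean change.

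The result before any loss is: "With a 1:1 trial-to-control ratio, each group requires 30 participants". The allowance for loss follows: "Strict quality control during the trial will limit the loss to follow-up rate to 20%, resulting in a total study sample of 72 participants", divided as 36 and 36.

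The total of 72, the 36 per group, or both recur in the Abstract and in sections 2.1, 2.2.7 and 2.3, so these are the numbers the trial works to. No formula for the loss allowance is given anywhere.

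**The concern.** The section prints the number needed, the loss rate and the number to be enrolled, and the third does not follow from the first two. If 20% of those enrolled are lost, fewer than 30 per group remain. The article's condensed form does not explain this, because nothing is missing: all three figures are on the page, and one multiplication shows that they disagree.

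Two things are at stake. The stated 90% power is attached to 30 per group, so the plan should show what remains of it at the loss rate it plans for. And the sentence will probably be carried into the final report, where any reader can check it.

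**Working it through.** **Inputs (all from section 2.2.6).** Mean change 6.6 (SD 4.2) with acupuncture and 3.2 (SD 3.7) with sham; one-sided α 0.025; power 90%; 1:1 allocation; 30 per group before loss; 20% loss; 36 per group and 72 in total after the allowance.

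**Step 1: reproduce the 30.**
- Difference: 6.6 − 3.2 = 3.4.
- Common SD: √[(4.2² + 3.7²)/2] = √15.665 = 3.958.
- Normal approximation: n = 2 × SD² × (z₀.₉₇₅ + z₀.₉₀)² / difference² = 2 × 15.665 × (1.960 + 1.282)² / 3.4² = 28.48, so 29 per group.
- Two-sample t-test (noncentral t, df = 2n − 2, noncentrality = 3.4 / [3.958 × √(2/n)]): power 89.5% at n = 29 and 90.5% at n = 30. The smallest n that reaches 90% is 30.

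The printed 30 is therefore reproduced by the t-test, without using δ.

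**Step 2: apply the loss allowance.**
- To keep 30 after 20% loss: 30 / (1 − 0.20) = 37.5, so 38 per group and 76 in total (75 if the total is inflated in one step, 60/0.80). Check: 38 × 0.80 = 30.4.
- The printed figure: 30 × 1.2 = 36 exactly, total 72.
- What 36 leaves at 20% loss: 36 × 0.80 = 28.8 per group, or 57.6 of 72 against the 60 required.
- Loss that 36 tolerates while keeping 30: (36 − 30)/36 = 16.7%.

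**Step 3: effect on power** (difference 3.4, SD 3.958, one-sided 0.025).

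| Evaluable per group | t-test | Normal approximation |
|---|---|---|
| 30 | 90.5% | 91.4% |
| 29 | 89.5% | 90.5% |
| 28.8 (expected at 20% loss) | 89.3% | 90.3% |
| 28 | 88.4% | 89.5% |

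By the t-test, the drop from 30 is 90.5 − 89.3 = 1.2 points at the expected number and 90.5 − 88.4 = 2.1 points if the number is rounded down to 28.

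**The case against.** The best defence is that 72 is about right on the plan's own inputs. The unrounded normal-approximation size is 28.48, and 28.48/0.80 = 35.6, which rounds up to 36. By that route 36 per group does give 90% power after a 20% loss. This stands as an argument that the trial is not materially underpowered. It does not rescue the sentence, because section 2.2.6 gives 30 as the requirement, and 36 does not follow from 30 by dividing by 0.80.

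A second defence is that the text says quality control will hold loss to 20%, which reads as a ceiling. The shortfall appears only if loss exceeds 16.7%. That is fair. Still, an allowance is meant to cover the rate it names, and this one does not.

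Three stronger readings are tempting, and the document does not support them:
- **That the trial falls below 90% power.** This depends on the formula. It does by the t-test, but the normal approximation gives 90.3% at 28.8 per group, and section 2.2.6 does not name its method.
- **That multiplying by 1.2 is an established fact.** The exact match makes it likely, but no formula is printed.
- **That power is really in the low seventies.** That results from treating δ as a superiority margin of 0.68 (one fifth of 3.4). The role of δ is unclear: the text says 5%, and one fifth of 6.6 would be 1.32. Even with 0.68, t-test power is already 74.5% at 30 per group and 72.7% at 28.8. Nearly all of that fall comes from the margin and under 2 points from the loss allowance, so it is a separate question.

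**Conclusion.** The inconsistency is real and minor. With 30 evaluable per group required and 20% loss, 36 per group leaves 28.8. Meeting the requirement would take 38 per group, 76 in total: 2 more per group and 4 overall. Power at 20% loss is about 88–90%, depending on rounding and formula, against 90.5% at 30 per group by the t-test.

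This takes the pilot means and SDs as given, a comparison of mean changes between two groups with no margin, and loss counted as a share of those enrolled and equal in both groups. The shortfall of 1 to 2 per group does not depend on how the 36 was obtained. A reader might infer that the design fails or that 72 has to be raised; a difference of one to two points of power does not support that.

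**What to change.** Keep 72 and restate the sentence in section 2.2.6 in one of two ways:

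- *36 per group leaves 30 evaluable with up to 16.7% loss*; or
- *with 20% loss about 28–29 per group are evaluable, giving about 88–89% power (t-test) for a 3.4-point difference.*

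It would help to name the formula behind the 30 in the same sentence. Any analysis plan that repeats the sample size should carry the same wording. Enlarging to 38 per group (76 in total) is optional and would keep the 20% figure as written.

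The cost of restating is one sentence and a slightly less favourable stated loss or power. The design, the analysis and the recruitment target stay as they are.

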#### Randomization and allocation

2.2.7

The trial will use simple randomization with a 1:1 allocation ratio between the treatment and control groups. Random assignment codes were generated by a statistics professional using SPSS software (Chicago, IL, USA) to create a random number grouping table. During implementation, enrolled participants will be assigned to corresponding groups for intervention and observation based on the sequential numbers in the randomized coding table. Participants will be randomly divided into a treatment group (acupuncture) and a control group (sham acupuncture). A total of 72 participants will be observed. Grouping information will be numbered sequentially and hidden by opaque, and sealed envelopes.

#### Blinding

2.2.8

In this study, the acupuncture practitioners will be not blinded, while the participants, outcome data collectors, statistical analysts, and outcome assessors will be blinded. Both the acupuncture group and the sham acupuncture group underwent skin penetration, but the location and depth of the acupuncture will be different. Participants will be in separate rooms, positioned supine for acupoint selection, with curtains drawn below the head to obstruct their view of the specific acupuncture locations. Additionally, appointments will be scheduled for the acupuncture sessions to prevent conversations among the participants.

Participants will be informed prior to randomization: You have a 50% chance of being assigned to either the traditional acupuncture group (deeper needle insertion) or the modern acupuncture group (shallow needle insertion). After the final treatment session at Week 12, each participant will complete a questionnaire asking, “Did you receive traditional acupuncture?” with response options of “Yes,” “No,” or “Uncertain.” Ultimately, Bang’s blinding index and James’s blinding index will be used to assess whether participants could distinguish between receiving real acupuncture or sham acupuncture (23, 24).

### Intervention

2.3

Participants will be randomly assigned to either the acupuncture group or the sham acupuncture group using a random number table, with 36 participants in each group. Acupuncture procedures will be performed by registered traditional Chinese medicine (TCM) physicians from Xiyuan Hospital, China Academy of Chinese Medical Sciences with at least 3 years of clinical experience and trained to treat participants in accordance with the study protocol. Treatments will be conducted in a room maintained at a constant temperature of 26 °C, with participants lying in a supine position. To ensure privacy, each participant will use an individual treatment bed separated by curtains.

#### Lifestyle intervention

2.3.1

Both the acupuncture group and the sham acupuncture group will receive health education upon enrollment, including suggestions from the researchers to maintain a regular diet, engage in appropriate exercise (Participants will choose a suitable form of exercise and persist with it; Participants will be recommended a combination of aerobic and resistance training, ensuring each session lasts at least 30 min and is performed at least twice a week), maintain good sleep habits, and avoid prolonged sitting (participants will be advised to get up and move for 10–20 min after every 1–2 h of sitting, with no single sitting session exceeding 2 h; they will also be suggested to sleep before 23:00 pm daily, minimizing or avoiding staying up late).

In addition, participants will be suggested not to take or use any Chinese herbal preparations (such as Shengjing Capsules, Qilin Pills, Compound Xuanju Capsules, etc.), health supplements (such as Vitamin E, Coenzyme Q10), drugs (such as L-carnitine, aromatase inhibitors, hormonal drugs, metformin, liraglutide, semaglutide, etc.), or any other health supplements, weight-loss teas that may affect semen quality or body weight from the researcher’s assessment. Additionally, participants will also be advised to avoid hot water sitz baths, moxibustion, acupoint embedding, and physiotherapy during the study period.

#### Acupuncture group

2.3.2

We will select bilateral ST36 (Zusanli), bilateral SP6 (Sanyinjiao), CV4 (Guanyuan), CV3 (Zhongji), bilateral KI12 (Dahe), and bilateral KI3 (Taixi) as the treatment acupoints (Figure 2). All acupoints’ location are in Table 2 and Figure 2. They are localized according to the World Health Organization Standard Acupuncture Point Location (24). The 0.3 mm × 40 mm stainless steel milli-needle (Huacheng Brand, Beijing Keyuanda Medical Devices Co., Ltd.) will be used for acupuncture. During the procedure, the acupuncturist should insert the needle gently and slowly until the tip reaches the expected depth. The needle will be manipulated every 10 min with 30 s each time to achieve the deqi sensation. The treatment will span 12 weeks (twice a week, with no less than 2 days between each pair of acupuncture sessions). And each acupuncture session will involve retaining the needle for 30 min.

**FIGURE 2 F2:**
[figure not shown]
Anatomical locations of acupuncture and sham acupuncture acupoints. Created in BioRender. [name] (2026) https://BioRender.com/nqr7qrs.

**TABLE 2 T2:** Intervention in the acupuncture group.

Acupoints	LocationInsert angle	Insert depth
ST36 (Zusanli)	3 cun below ST35 (Dubi), one finger-breadth from the anterior crest of the tibia.90°	2 cun
SP6 (Sanyinjiao)	3 cun directly above the tip of the medial malleolus, on the posterior border of the tibia.90°	1.5 cun
CV4 (Guanyuan)	Front median line of the body, 3 cun below the middle of the navel90°	1.5 cun
CV3 (Zhongji)	Front median line of the body, 4 cun below the middle of the navel90°	1 cun
KI12 (Dahe)	Front median line of the body, 4 cun below the middle of the navel, 0.5 cun next to the anterior median line90°	1 cun
KI3 (Taixi)	Medial side of the foot, depression between the posterior aspect of the medial ankle and the tendon of the heel bone90°	1 cun

#### Sham acupuncture group

2.3.3

The procedure for sham acupuncture will adhere to the protocol outlined in our previous article (25, 26). Participants will assume a supine posture and undergo standard localized disinfection. Subsequently, the 0.3 mm × 25 mm stainless steel milli-needle (Huacheng Brand, Beijing Keyuanda Medical Devices Co., Ltd.) will be inserted at the acupoint without deqi sensation. Both needle retention time and the overall treatment period will match those applied in the acupuncture group. Specific manipulations will be performed by the acupuncturist: 10 mm lateral to the ST36 (Zusanli), 2–3 mm straight stab; 10 mm anterolateral to the SP6 (Sanyinjiao), 2–3 mm straight stab; 10 mm posterior to the KI3 (Taixi), 2–3 mm straight stab; 5 mm lateral to the KI12 (Dahe), 2–3 mm straight stab; 15 mm lateral to the CV3 (Zhongji), 2–3 mm straight stab; and 15 mm lateral to the CV4 (Guanyuan), 2–3 mm straight stab (Figure 2).

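### In the lower abdomen the sham CV3 and KI12 sites lie close to treatment point KI12, and the participant script names needle depth as the mark of each arm

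*Protocol article*

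**What the plan says.** **Location.** Section 2.2.8 (Blinding) says both arms involve skin penetration but "the location and depth of the acupuncture will be different". Section 2.3.2 lists KI12 as a bilateral treatment point and CV3 as a single one. Table 2 places CV3 on the midline, 4 cun below the navel, and KI12 "4 cun below the middle of the navel, 0.5 cun next to the anterior median line". Section 2.3.3 (Sham acupuncture group) places the sham needles "5 mm lateral to the KI12 (Dahe), 2–3 mm straight stab" and "15 mm lateral to the CV3 (Zhongji), 2–3 mm straight stab". The remaining sham sites are 10 mm from ST36, SP6 and KI3 and 15 mm from CV4. The sentence in section 2.3.3 that introduces these offsets describes the sham needle as going in at the acupoint itself.

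**Masking.** Section 2.2.8 counts participants among those blinded. It also has them told before randomisation that they have an even chance of entering the "traditional acupuncture group (deeper needle insertion) or the modern acupuncture group (shallow needle insertion"). After the last session at week 12 they are asked whether they received the traditional form. Their answers feed the Bang and James blinding indices.

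**The concern.** A sham site moved sideways from one treatment point should not end up near another. CV3 and KI12 lie on the same horizontal line, and KI12 is needled on both sides. Moving the CV3 needle laterally therefore takes it towards a KI12 point, whichever side is used. If a penetrating control needle sits close to a treatment point, the location part of the contrast is weakened there, and a null result becomes harder to interpret.

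The second issue is separate. Curtains block sight but not sensation. Depth is something a participant may be able to feel, and the script tells him which group each depth belongs to. A participant who works out his arm may behave differently in ways that could affect semen quality; exercise, for example, is only advised (section 2.3.1). The blinding index would then partly measure a cue that the trial itself supplied.

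**Working it through.** The article states no distance between sham CV3 and KI12, so there is no stated figure to reproduce. The distances follow from the layout.

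**Inputs**
- CV3: midline, 4 cun below the navel (Table 2).
- KI12: same level, 0.5 cun from the midline, bilateral (Table 2; section 2.3.2).
- Sham CV3: 15 mm lateral to CV3; sham KI12: 5 mm lateral to KI12 (section 2.3.3).
- c, the length of 1 cun in mm: not given, so treated as an assumption and varied.

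**Formulas** (distance from the midline, same side)
- KI12: 0.5c.
- Sham CV3: 15.
- Sham KI12: 0.5c + 5.
- Sham KI12 to KI12: (0.5c + 5) − 0.5c = 5 mm for every c.
- Sham CV3 to KI12: |15 − 0.5c|.
- Sham CV3 to sham KI12: |15 − (0.5c + 5)| = |10 − 0.5c|.

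**Results (mm)**

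| c | KI12 from midline | Sham CV3 to KI12 | Sham CV3 to sham KI12 |
|---|---|---|---|
| 15 | 7.5 | 7.5 | 2.5 |
| 18 | 9 | 6 | 1 |
| 20 | 10 | 5 | 0 |
| 25 | 12.5 | 2.5 | 2.5 |
| 30 | 15 | 0 | 5 |
| 40 | 20 | 5 | 10 |
| 45 | 22.5 | 7.5 | 12.5 |

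Sham CV3 is within 5 mm of KI12 exactly when c lies between 20 and 40.

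**Internal bound on c.** Table 2 gives a depth of 2 cun at ST36, and section 2.3.2 gives a 40 mm needle. If that depth is to be reached, 2c ≤ 40, so c ≤ 20. This assumes that cun means the same length for depth as for location. Under the bound, sham CV3 is 5 mm or more from KI12. At c = 20 it falls on the sham KI12 site of the same side, since both are 15 mm from the midline.

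**Wording.** Section 2.2.8 says location differs. The lead-in of section 2.3.3 puts the sham needle at the acupoint, and the list that follows gives offsets of 5 to 15 mm. The lead-in cannot be read literally alongside the other two statements.

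**Masking.** What can be felt differs: insertion of 2–3 mm without deqi (section 2.3.3), against 1 to 2 cun with manipulation for 30 s every 10 min (section 2.3.2; Table 2). This is repeated over 2 × 12 = 24 sessions. The script links depth to a group name, and the week-12 question asks about that name.

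**The case against.** Several objections are sound and limit the point.

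- **The whole sham arm.** A reader might infer that the sham is not off-point at all. The documents do not support that. The ST36, SP6, KI3 and CV4 shams are 10 to 15 mm from their own points, and depth and deqi differ at every site.
- **Exact coincidence.** A reader might infer that sham CV3 lands on KI12. That requires c = 30, which the needle-length bound excludes.
- **Contradiction.** An offset of 5 mm is, literally, a different location, and section 2.2.8 sets no minimum distance. The acupoint wording may be a loose lead-in. Figure 2 may settle part of this but is not reproduced in the text at hand. The point is therefore poor separation and wording to reconcile.
- **Lost power.** It is tempting to assume a dilution fraction and compute a power loss. Nothing in the documents supports any fraction. The planning difference of 6.6 − 3.2 = 3.4 (section 2.2.6) was already measured against sham, so any activity of a similar sham may already be in the 3.2.
- **Behaviour after unmasking.** A reader might infer that adherence and supplements rest on advice alone. Section 2.2.5 makes poor compliance, missed acupuncture and use of interfering drugs grounds for termination. Exercise is the clearer example of something only advised.
- **Failed masking.** Neither option is called sham, both penetrate the skin, the view is blocked, participants are kept apart, and each man experiences only one technique. Data collectors, assessors and analysts are blinded. The cue shows which technique was given, not that it is a control.

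The 5 mm offset at KI12 still stands, as do the undefined cun on which the CV3 site depends and a depth cue that the trial does not need to give. The blinding indices measure unmasking after the event; they do not prevent it.

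**Conclusion.** The point holds for the lower abdomen and for the script, not for the sham arm as a whole. Sham KI12 is 5 mm from KI12 whatever the cun. Sham CV3 is 0 to 5 mm from KI12 if 1 cun is 20 to 40 mm, and farther outside that range (7.5 mm at 15 or 45 mm). Under the article's only internal bound, c ≤ 20, it is at least 5 mm away, but at c = 20 it coincides with sham KI12. The range for c is an assumption, and the bound assumes one cun for both depth and location.

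The script creates an avoidable risk to masking. Neither its effect nor that of the close sham sites can be quantified from the documents. Close sham needling would tend to shrink the contrast, while unmasking could bias it through behaviour. The sample size is unaffected. Both matters are cheap to correct and worth correcting.

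**What to change.** 1. Reconcile sections 2.2.8 and 2.3.3, Table 2 and Figure 2 on the sham CV3 and KI12 sites, and state the cun-to-millimetre conversion used. The choice of sites belongs to the acupuncture team.
2. Reconcile the lead-in wording of section 2.3.3 about the acupoint with the listed offsets and with section 2.2.8.
3. Remove the two parenthetical remarks on depth from the participant script and say only that two needling techniques are compared. How much to disclose is also a consent matter, so the ethics committee must agree the wording.
4. Record the date of each change.

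**Cost.** An ethics amendment and brief retraining of the two practitioners. Participants enrolled before the change will have been treated under the old site description and script, which is why the date must be recorded. Recruitment is planned to run to October 2026 and the article appeared in March 2026, so on that schedule later participants could still benefit.

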### Outcome measures

2.4

#### Primary outcome measure

2.4.1

Progressive sperm motility (PR) refers to the proportion of sperm in semen that can move in a straight line or with a larger radius, which is an important indicator for assessing sperm motility. We will assess the PR at week 12 as the primary outcome.

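### The primary outcome is PR at week 12, but the trial is sized on change in PR from baseline, so the stated 90% power is shown only for the change score

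*Protocol article*

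**What the plan says.** Two sections of the protocol article describe the primary variable differently.

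- Section 2.4.1 (Primary outcome measure): "We will assess the PR at week 12 as the primary outcome". Neither change nor baseline is mentioned.
- Section 2.2.6 (Sample size consideration): "Sample size calculations were based on the primary efficacy indicators, estimated as the change in PR from baseline at week 12 of treatment". The inputs are changes too: "acupuncture treatment for asthenozoospermia yielded a mean percentage change of 6.6 ± 4.2" and "sham acupuncture treatment showed a mean change of 3.2 ± 3.7". The result is "With a 1:1 trial-to-control ratio, each group requires 30 participants", raised to 36 per group for loss to follow-up.

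Section 2.5.2 (Data analysis) lists rank-sum tests, chi-square tests and repeated measures ANOVA with a Greenhouse–Geisser correction. It does not say which of these tests PR at week 12, and it names neither a baseline covariate nor a change-score analysis. Table 1 schedules PR at week 0 and at weeks 4, 8, 12, 18 and 24. Section 2.4.2 does refer BMI, waist-to-hip ratio and body fat percentage to baseline, so the article makes that reference for some outcomes but not for PR.

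**The concern.** PR at week 12 and change in PR to week 12 estimate the same between-group difference under randomization, but with different precision. The SDs in section 2.2.6 are SDs of change. They do not give the SD of week-12 PR, which also depends on how strongly baseline and week-12 PR are correlated. A power statement for one variable therefore does not carry over to the other.

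Three things are at stake:

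- The power of the headline comparison is unknown if section 2.4.1 is taken literally.
- Section 2.2.7 specifies simple randomization without stratification. A chance baseline difference in PR would pass, in proportion to the correlation, into an unadjusted week-12 comparison.
- Two descriptions of the primary variable leave room to choose between them after the data are seen. This matters whatever the correlation is.

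**Working it through.** **Inputs.** From section 2.2.6: mean changes 6.6 and 3.2, SDs of change 4.2 and 3.7, one-sided α 0.025, power 90%, 30 per group. The SD of week-12 PR and the baseline-to-week-12 correlation ρ are not given, so they are varied below as assumptions.

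**Step 1: reproduce the planned number.**

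- Difference: 6.6 − 3.2 = 3.4.
- Pooled SD of change: √((4.2² + 3.7²)/2) = √15.665 = 3.96.
- Normal approximation: n = 2 × (1.960 + 1.282)² × 15.665 / 3.4² = 28.5, so 29 per group.
- The t-test version gives 29.5, so 30 per group. Power at 30 per group is 90.5%.

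The stated 30 is reproduced as a plain superiority comparison of change scores. The δ of 5% in the same section is not needed to reach it; used as the difference to detect, it would give 14 per group.

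**Step 2: what the change SD implies for week-12 PR.** With equal SD s at both visits, SD of change = s√(2(1 − ρ)), so s = 3.96/√(2(1 − ρ)). This equals 3.96 at ρ = 0.5, is smaller below that and larger above it. ANCOVA on baseline has residual SD s√(1 − ρ²).

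**Step 3: power at 30 per group for a 3.4-point difference** (t-test; required n by normal approximation).

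| ρ (assumed) | SD of week-12 PR | Power, unadjusted | n per group for 90%, unadjusted | ANCOVA residual SD | Power, ANCOVA |
|---|---|---|---|---|---|
| 0.3 | 3.35 | 97.2% | 21 | 3.19 | 98.2% |
| 0.5 | 3.96 | 90.5% | 29 | 3.43 | 96.5% |
| 0.6 | 4.43 | 83.3% | 36 | 3.54 | 95.5% |
| 0.7 | 5.11 | 71.7% | 48 | 3.65 | 94.4% |
| 0.8 | 6.26 | 54.4% | 72 | 3.75 | 93.2% |
| 0.9 | 8.85 | 31.0% | 143 | 3.86 | 91.9% |

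The change score stays at 90.5% in every row, because its SD is held at the pilot value.

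**Step 4: why ANCOVA is not worse than either.** Let s₀ and s₁₂ be the SDs at week 0 and week 12. The ANCOVA residual variance is s₁₂²(1 − ρ²), which cannot exceed s₁₂². The variance of change is s₀² + s₁₂² − 2ρs₀s₁₂ = s₁₂²(1 − ρ²) + (s₀ − ρs₁₂)², which cannot be smaller than the ANCOVA variance. This ordering does not need equal variances. ANCOVA costs one degree of freedom, which is negligible here.

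**Step 5: chance imbalance.** At ρ = 0.8 the standard error of the baseline difference with 30 per group is 6.26 × √(2/30) = 1.6 points, nearly half of the 3.4-point effect.

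**The case against.** The strongest reply is that the two sections can be read together. Section 2.4.1 names the measure and the visit, section 2.2.6 supplies the metric, and nowhere does the article call the outcome raw or unadjusted. That is a fair reading, and it makes this an inconsistency to reconcile rather than a settled choice of unadjusted PR. But the text does not force it, and the primary variable should not have to be inferred from the sample size section.

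A reader might infer that the trial is underpowered on its stated endpoint. The documents do not support that. Power on week-12 PR could be above or below 90%, since neither the SD nor the correlation is given. Section 2.2.2 requires PR below 32% on two or more analyses, which restricts the baseline range and may lower the correlation. The break-even of 0.5 itself assumes equal variances; in general week-12 PR has the larger SD when ρ > s₀/(2s₁₂). If entry restriction makes s₀ smaller than s₁₂, the break-even falls as well, so the net direction is unclear.

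A reader might also infer that no planned analysis takes baseline into account. That is too flat. Repeated measures ANOVA could include week 0 as a level, in which case the group-by-time term would use it, and model detail may sit in an analysis plan that is not shown. What stands is that section 2.5.2 does not say week 0 is included and does not name this ANOVA as the test of the week-12 outcome. With all six visits in the model, the interaction would be an omnibus test rather than the week-12 contrast for which the trial was sized.

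Finally, both sections could simply be aligned on change from baseline. That would cure the contradiction, but it gives up precision that ANCOVA offers without further data.

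**Conclusion.** The point holds as a mismatch within the article: the stated primary outcome and the powered variable differ, and no named analysis uses baseline PR as a covariate. The 90% power is shown for the change score only. For an unadjusted comparison of week-12 PR at 30 per group, the plausible range is wide: about 97% at ρ = 0.3, 90.5% at 0.5, 72% at 0.7 and 54% at 0.8. These figures assume equal variances at both visits, a true difference of 3.4 points and the pilot SDs of change. They show that a loss is possible, not that there is one.

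The case for the change does not depend on which correlation is true. Baseline-adjusted analysis keeps at least the planned change-score power throughout the range examined, accounts for chance imbalance in baseline PR and closes the choice between two primary variables. It is best regarded as a free improvement.

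**What to change.** Use one definition in sections 2.2.6 and 2.4.1, and name the matching analysis in section 2.5.2. Suggested wording: the primary outcome is PR (%) at week 12; the treatment effect is the between-group difference in mean week-12 PR adjusted for week-0 PR, estimated by ANCOVA with group and baseline PR as terms, and reported with a 95% confidence interval.

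In section 2.2.6, keep the calculation but say that the SD of change was used as a conservative basis for the adjusted analysis. Present unadjusted week-12 means and mean changes descriptively. With baseline PR in the model, analysing week-12 PR or its change from baseline gives the same group effect, so the two present descriptions then lead to one result.

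The cost is wording in the protocol and the analysis plan, to be settled before unblinding. Week-0 PR is already scheduled in Table 1, so no visit, measurement or participant is added.
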